**Fit Moms/**
***Mamás Activas***
**cluster randomized design.**

### Clinic and participant recruitment

A total of 12 clinics (six in Santa Barbara county, four in San Luis Obispo county, and two in Ventura county) were selected for inclusion in this study. The clinics were selected because they are representative of California state WIC populations, are willing to accept randomization, and agreed to the study’s recruitment and intervention protocols. At these clinics, a combined total of 408 participants (34 per clinic) are targeted for recruitment. Blinded study research assistants are screening woman attending their postpartum visits, using our pre-established screener [71,72]. Women who appear interested in the program are asked to complete a permission to be contacted card and are then screened by phone; phone screening is done (rather than on-site screening) to ensure patient privacy and limit potential burden on WIC clinics of requiring private screening rooms during recruitment. If still eligible after screening, patients will be asked to attend an orientation meeting, complete informed consent, and are scheduled for baseline screening visits. Once sample sizes are met at a given clinic, recruitment is closed at the clinic. The flow chart of these stages of recruitment is shown in Figure 2.

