### Randomization and masking

Randomization is computer-generated by the statistician. Specifically, randomization is conducted at the clinic level, stratified by county, and designed to ensure balance in treatment arms. Four clinics were crossed-over (in random order) in order to allow for estimation of some within-clinic effects. We decided to stratify randomization by county to control for any chance imbalance due to potentially unmeasured regional or administrative differences. We decided against further stratifying based on ethnicity and pre-pregnancy BMI due to the small likelihood of a chance imbalance, given the demographic similarity of the clinics, and limited evidence that these variables impact treatment response among postpartum (or other) women [83,84]. Within each randomized clinic, participants are sequentially selected until target sample sizes are met (please see Sample size calculation section**).**

Recruiters and assessors are blinded to the clinic randomization, and participants are not told their assigned treatment status until after enrollment. Several procedures are in place to ensure blinding among clinic recruiters, assessors, and potential enrollees. In brochures and the study consent form, the study is presented identically at both control and intervention clinics. There is a minimal amount of cross-over activity between clinics, but the study’s branded items are distributed at both intervention and control clinics as part of retention so that the study logo is a familiar sight. The recruiters and assessors have little to no contact with individuals aware of treatment assignment, including the WIC county chiefs and intervention research assistants.

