### Institutional and interpersonal level intervention

#### Brief clinic visits

WIC public health aides and dietitians spend five minutes during patients’ regularly scheduled WIC visits (typically every three months) to reinforce use of the internet-based program. After WIC practitioners logon to the WIC check-in system, they receive an alert and instructions to provide the patient with a specific Fit Moms/*Mamás Activas* color-coded card, tailored to each patient’s level of adherence to logging on to the website and attending groups. The WIC counselors review the cards and encourage patients to use the Fit Moms/*Mamás Activas* site and to attend groups. We considered allocating a greater role for the WIC practitioners at these visits (such as discussing weight loss progress, goal setting, problem solving, and motivation interviewing). However, the scripted message and simplicity of the protocol were praised by the WIC staff during our design phase and have been designed to fit into the busy WIC practice setting, provide institutional-level support for the intervention, and enable delivery by both public health aides and dietitians. More extensive professional support is provided by study interventionists at monthly groups.

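### Women are recruited after their clinic is allocated, and the recruiter blind that guards against selection is inadequately protected: front-line WIC staff who know the arm work where recruiters screen

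*Protocol article*

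**What the plan says.** All references are to the protocol article.

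- **Order of events** (Randomization and masking): "Within each randomized clinic, participants are sequentially selected until target sample sizes are met". Allocation is by clinic and precedes recruitment.
- **Claimed blind** (same section): "Recruiters and assessors are blinded to the clinic randomization, and participants are not told their assigned treatment status until after enrollment". On separation from informed people it adds: "The recruiters and assessors have little to no contact with individuals aware of treatment assignment". Two groups are given as examples: the county chiefs of WIC, and the research assistants who work on the intervention.
- **Where recruiters work** (Clinic and participant recruitment): "Blinded study research assistants are screening woman attending their postpartum visits, using our pre-established screener". Women who seem interested are asked for a card permitting contact. The next step is by telephone: "phone screening is done (rather than on-site screening) to ensure patient privacy and limit potential burden on WIC clinics".
- **Who delivers the intervention in the clinic** (under Brief clinic visits, first sentence): "WIC public health aides and dietitians spend five minutes during patients’ regularly scheduled WIC visits (typically every three months) to reinforce use". What they reinforce is the online program. After logging on to the check-in system, "they receive an alert and instructions to provide the patient with a specific" color-coded study card, and they encourage website use and group attendance.
- **Related statements.** Study design gives clinicians' reinforcement of the intervention as one reason for randomising clusters. The description of the standard WIC group says that WIC visits are run by nutritionists or public health aides.

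**The concern.** In a cluster trial that recruits after allocation, randomisation balances the clinics but not the women who are approached and agree to join. Comparability of the women depends on recruiters, and the women themselves, not knowing the arm. The article claims that separation, but names only two groups of informed people and leaves out the one that recruiters are most likely to meet.

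If a recruiter or a prospective participant picked up the arm, women keener on a web and group program could be over-represented at intervention clinics. Motivation to lose weight is not among the covariates named in the Analysis plan, so adjustment could not be relied on to remove the difference. Any such difference would enter the primary weight contrast directly, and a larger sample would not reduce it.

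**Working it through.** **The sections side by side**

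1. Recruitment follows allocation (Randomization and masking), so masking matters for who enters the trial as well as for outcome assessment.
2. Aides and dietitians at intervention clinics receive alerts, hand over cards and encourage use of the program (Brief clinic visits). They must therefore know the arm.
3. The same categories of staff run ordinary WIC visits (description of the standard WIC group).
4. Recruiters screen women attending visits at the clinics (Clinic and participant recruitment).
5. From 2 to 4, recruiters work in a setting staffed by people who know the arm. The claim in Randomization and masking is hard to square with this, and no section says how the two are kept apart.
6. Each stated safeguard against this gap:
   - Identical brochures and consent forms, and branded items in both arms, mask study materials. They do not mask alerts, cards or staff conversation.
   - Late disclosure to participants controls what the study tells them. It does not control what recruiters learn.
   - Phone screening is justified by privacy and clinic burden, and it comes second. The earlier on-site step already picks out women who seem interested, so discretion can enter there.

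**The plan's own figure**

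Inputs from Sample size calculation: 12 clinics (taken as 6 per arm), 34 women per clinic, 30% attrition, SD 4.5 kg, ICC 0.02, difference 2 kg, two-sided 0.05. The four cross-overs are ignored.

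- Completers per clinic: 34 × 0.70 = 23.8
- Design effect: 1 + (23.8 − 1) × 0.02 = 1.456
- Effective n per arm: 6 × 23.8 / 1.456 = 98.1
- SE of the difference: 4.5 × √(2/98.1) = 0.643 kg
- Power for 2 kg: 87.5% (normal approximation) or 80.1% (t, 10 df)

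The stated power of at least 80% is reproduced, and the masking point does not alter it.

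**Illustration only**

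Assume that selective recruitment shifts the arm difference by b kg and that there is no true effect. The documents give no value for b, so a range is shown. The rejection rate under the normal approximation is Φ(b/SE − 1.96) + Φ(−b/SE − 1.96). The t version uses the noncentral t with 10 df.

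| b (kg) | b as share of 2 kg | Rejection, normal | Rejection, t (10 df) |
|---|---|---|---|
| 0.25 | 12.5% | 6.7% | 6.4% |
| 0.50 | 25% | 12.2% | 10.9% |
| 0.75 | 37.5% | 21.5% | 18.5% |
| 1.00 | 50% | 34.3% | 29.1% |

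The table shows what would follow from a shift of a given size. It is not evidence that a shift occurs.

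**The case against.** The case for the protocol has real weight.

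- No section reports that a recruiter learned an allocation, or that a woman learned hers before consent.
- Recruiters are study staff, not WIC staff, and use a set screener.
- The alert appears in the WIC check-in system. The card goes to a woman already enrolled, in a five-minute exchange typically every three months. Nothing says that recruiters see either.
- Groups are closed to newcomers and led by study staff.
- The article does not say how far recruitment and delivery overlap in time at a clinic. Overlap is a reasonable inference, since enrolment is sequential, the intervention lasts 12 months and nothing holds delivery until recruitment closes, but it remains an inference.
- The Analysis plan allows adjustment for baseline differences, and partial proxies for motivation are collected (self-efficacy, history of intentional weight loss).
- The two named groups are examples, and a condensed article may leave operational detail to the full protocol.

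These points rule out stronger readings. A reader might infer that the blind must fail, or that selection is in effect open; the documents show neither. A reader might also infer that one cue exposes the arm of every later woman at a clinic. Four of the 12 clinics cross over, so that is not generally true.

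The last point, on operational detail, does not dispose of the matter. The article makes a positive statement about separation and elsewhere describes an arrangement that undercuts it. That is a conflict within the text, not merely an omitted detail.

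**Conclusion.** The point holds in a limited form. Recruitment follows allocation, front-line WIC staff at intervention clinics know the arm, and recruiters work at visits in those clinics. The masking statement conflicts with the sections on study design, recruitment and brief clinic visits. The recruiter blind is at risk and inadequately protected as described, so selection bias after allocation cannot be excluded.

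Neither the size nor the direction of any bias can be derived from the documents. The error rates above rest on an assumed shift and on treating the trial as six parallel clinics per arm. The sample size does not need to change. The point should be dealt with while recruitment continues, which the article says is expected to last until December 2015.

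**What to change.** 1. **On site:** recruiters offer the contact-permission card to consecutive attending women, without judging interest or suitability.
2. **By phone:** existing study staff carry out the planned phone screen in card order, without seeing the clinic name.
3. **Masking statement:** amend Randomization and masking to say that front-line WIC staff at intervention clinics are unmasked, and reconcile it with Study design and Brief clinic visits.
4. **Reporting:** give the proportions approached, eligible, declining and consenting, and baseline characteristics, by arm. At the four crossed-over clinics, count each woman under the arm in force when she was recruited. This extends the tracking already described under Assessment of recruitment, attrition, and referral rates; a log of all women approached may be the only new record.

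Steps 1 and 2 protect only women still to be recruited; for those already enrolled, step 4 is the available check. The cost is slightly more logging, possibly slower recruitment, and a masking claim that is weaker but accurate. The primary analysis is unchanged.

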### Experimental conditions

#### Group one: standard Women, Infant and Children Supplemental Nutrition Program

The WIC program is a federal nutrition program for low-income women and their children that provides healthy foods, nutrition education, breastfeeding advice and support, and referrals. WIC clinics across the nation utilize a protocoled system for standardizing the frequency of contact and content of each patient-practitioner visit. At one to six weeks postpartum, women are seen by a WIC clinician, assessed, and assigned a contact code based on their breastfeeding status and health risk. The minimum frequency of contact, according to federal requirement, is five times during the first postpartum year (at six weeks, three months, six months, nine months, and 12 months) and at least four times during subsequent years (for example, 15 months, 18 months, 21 months, 24 months, and so forth). More frequent visits (one per month) may be offered during the first postpartum year to women who are at high risk (such as those who have medical problems or very limited income). Visits are conducted by nutritionists or WIC public health aides who provide nutrition counseling and referrals as needed, general support and guidance, and food vouchers. Women desiring to lose weight are advised to limit portions and increase activity; however, no structured weight control program is currently provided.

In Fit Moms/*Mamás Activas*, women randomized to standard care receive the standard WIC intervention plus a brief orientation to the study (to serve the purpose of bonding participants to the study) and study newsletters every two months with basic information about weight control, exercise, nutrition, and wellness.

#### Group 2: enhanced Women, Infant and Children Supplemental Nutrition Program plus internet-based weight control program

Patients in this group receive all elements of group one (standard WIC) plus an enhanced WIC and internet-based weight loss program. Given that it is now widely recognized that, to be effective, weight control treatment must be continued in long-term [85], we designed the intervention to continue for the duration of the trial (12 months). As noted earlier, our intervention is rooted in social learning theory and the social ecological model of behavior change and, thus, targets individual, interpersonal, and institutional levels, as outlined below.

### Individual level intervention: internet-based weight control program

#### Overview

Developed and evaluated in several interventions of up to one year by [name] *et al.* [49,50,86,87] this comprehensive, individually focused, SCT theory-driven, weight control program includes education, behavioral self-regulatory strategies, continuing contact, prompting, and access to social support. [name] *et al.* have examined this internet behavioral weight control program in several studies [50,87]. These effective online interventions are based on the Diabetes Prevention Program (DPP) and Look Ahead lifestyle interventions [88,89], which also have been proven effective in promoting long-term weight loss in multiethnic, low literacy, English- and Spanish- speaking individuals across the country [88,89]. Since the DPP and Look Ahead interventions involved individual meetings with treatment professionals, the online lessons and assignments were re-written to be more self-directed, and tailored to individuals’ needs through weekly assessments of progress upon login and programmed algorithms, rather than tailored by the human counselor. In Fit Moms/*Mamás Activas*, the intervention has been further adapted to fit needs of a postpartum, low-income, low literacy population; the website includes shorter written content, more pictures of pregnancy, mothers, and babies, and sleep and stress management components to address the challenges of caring for a baby and cooking on a budget while changing lifestyle behavior. Instructional lesson overviews and other videos provide information in a visual format.

#### Website

The website is not specific to one particular culture or dietary intake pattern, but rather attempts to provide guidance and resources that may be helpful to individuals from a variety of different cultures, incomes, and backgrounds. The website content is available in both English and Spanish and is accessible to each participant anywhere she has an internet connection. Each individual has a unique username and password. Participants can choose to log in at home, at work, or elsewhere. Patients are provided with a ‘technical assistance’ number to call should they encounter any difficulties in accessing the website. New content (lesson, tip, or link) is provided each week, but the site is designed to permit flexibility in the pace of presentation of new information. Participants are encouraged to login on Mondays to get new guidance, and then may check back periodically to see if new messages have been posted to the message board or to look for a specific link. This website was adapted from previous websites developed for research in [name] and colleagues [49,50,87] by NuMudia Productions Inc, Wake Forest, NC; USA.

#### Web Diary

Participants are encouraged to use an internet diary to look up foods and record intake. The diary (available in English or Spanish) is integrated with a comprehensive physical activity web diary. If patients are unable or unwilling to use the online diary, they are provided with paper diaries or encouraged to use alternative online tracking resources. Evidence-based strategies associated with lowering calorie intake are promoted, including following a simple, culturally relevant meal plan designed to be low cost and family-oriented.

#### Links

An organized directory of links is provided to quality diet-related sites (such as those that provide general nutrition, menu planning, recipes, and/or weight loss tips), exercise-related sites (such as those that provide lifestyle activities, information on overcoming barriers, and/or walking information), and behavioral and other sites (such as those that provide information on managing emotional eating) that are monitored by program staff for quality, relevance, and timeliness.

#### Weekly structured weight management lessons

Each lesson focuses on a topic related to weight regulation, eating, exercise, or behavior change strategies [88,89]. Each new behavioral lesson is summarized in a brief, introductory video and can also be viewed through on-screen text with visuals that may be printed for reference. Lessons are posted weekly for the intervention duration. Topics include: selecting appropriate calorie goals, modifying fat intake, increasing fiber, grocery shopping, label reading, restaurant eating, beginning exercise, aerobic fitness, self-monitoring, stimulus control, problem solving, social assertion, goal setting, body image, cognitive strategies for avoiding negative thinking and cognitive errors, overcoming barriers, relapse prevention training, strategies of successful weight losers in the National Weight Control Registry [90], and numerous other diet or exercise topics based on the DPP [84], and other weight, nutrition, and exercise projects.

#### Dietary goals

Participants are provided with sample meal plans and are instructed to follow a standard calorie restriction diet used in behavioral weight loss programs [84,88,89]. The meal plans include the option of using liquid meal replacements, but meal replacements are not provided as part of the intervention. Calorie goals are designed to produce a weekly weight loss of 0.5 to 1 kg and are based on study entry weight and breastfeeding status. Specifically, women whose current weight is under 91 kg, 91 to 115 kg, or over 115 kg are provided with 1,200 calorie per day, 1,500 calorie per day, and 1,800 calorie per day goals, respectively. Women who are exclusively breastfeeding are prescribed 300 additional calories per day. Participants are also instructed to reduce calories from fat to 35%, as calorie plus fat restriction has been shown to produce better weight loss than calorie restriction alone [91]. A diet rich in whole grains, fruits, vegetables, and lean meats or beans is encouraged, recognizing a variety of dietary choices and styles from different cultures, incomes, and backgrounds.

#### Exercise goals

Participants are instructed to gradually increase their physical activity to at least 30 minutes per day on most days of the week in moderate-intensity activities [84,88,89,92]. ‘Baby-friendly’ and inexpensive activities are suggested, taking into consideration women’s potentially unsafe neighborhoods. Walking is encouraged, but many different moderate-intensity exercises are suggested. Once participants reach 30 minutes per day on most days, they are encouraged to maintain or increase their total amount of exercise to between 60 and 90 minutes every day, as a higher level of physical activity may be necessary to achieve long-term weight loss maintenance [93-96].

#### Weight loss goals

Participants are given a scale and told to expect weight loss of 0.5 to 1 kg per week until reaching their weight loss goal. Women who are 10 pounds or more above their pre-pregnancy weight are encouraged to set an initial goal of getting back to their pre-pregnancy weight. Women who are within 10 pounds of their pre-pregnancy weight and overweight or obese are encouraged to set a 10% weight loss goal. Patients desiring to lose more weight are encouraged to do so, provided they maintain reasonable eating and activity patterns, and do not reduce below normal weight. Moderate weight loss does not appear to adversely affect lactation [23,74,75], but the study is monitoring such changes and tailoring goals accordingly.

#### Computer-tailored content and feedback

Each week upon participant login, the participant completes a check-in that inquires about weight loss progress and barriers to reaching goals. Responses are compared with pre-programmed algorithms to determine if progress is on track with expected weight loss, slow, or nonexistent. Tailored content (additional readings, links, and pdf tools), feedback, and recommendations are provided in a specific section of the website homepage based on progress and individual barriers.

#### Online message boards

From the study website, participants can access a secure, study-specific message board available in English or Spanish. The message board is designed to provide patients with opportunities for group support, problem solving, and feedback from study interventionists and peers. At any time, participants may post questions or comments. The board is moderated on a daily basis by study interventionists, who answer questions and provide feedback.

